**Figure 2 F2:**
[figure not shown]
**Timeline of the experimental protocol.** Monthly visits with the kinesiologist include the Beck Anxiety Inventory as well as health and habit questions.

### Interventions

#### Health habits intervention

Women in both groups will be given the *Sensible Guide to a Healthy Pregnancy*[25] created by the Public Health Agency of Canada*.* The guide contains information on the following health habits during pregnancy: nutrition, folic acid, alcohol consumption, physical activity, smoking, oral health and emotional health.

### Exercise intervention

Women randomly assigned to the exercise group will be asked to exercise a minimum of three times per week for 20 minutes each time at a minimal intensity of 55% of their VO_2_max, as per the protocol of Clapp and colleagues [15]. Intensity will be measured using the 6 to 20 Borg perceived exertion scale [26], given that it is accepted that 12 on the Borg scale corresponds to 55% of an individual’s VO_2_max [27].

### Measurements

#### Exercise intensity

Participants in the exercise group will perform a supervised exercise session on a cycle ergometer every month (Corival, Lode B.V., Groningen, The Netherlands) to learn the use of Borg’s perceived exertion scale. To allow the participants to easily identify the minimal intensity required for their at-home exercise, target intensity will correspond to 12 on the Borg scale (that is, 55% of their VO_2_max). The entire session will last 30 minutes, including a 5 minute warm up and a 5 minute cool down. Participants in the control group will be asked to complete a similar supervised session once per trimester to allow them to measure intensity in the event that they do exercise.

### Primary outcome measures

The MMN will be measured as early as 8 to 12 days after birth in order to isolate the effects of exercise during pregnancy from the possible effect of postpartum health habits. Brain activity will be recorded using the 124 electrodes Geodesic system of EGI Acquisition Systems (Eugene, Oregon, USA). Because this is safe, easy to install and provides good spatial resolution, it is commonly used in studies with newborns [28]. Electrode impedance will be kept below 50 kΩ, which is the recommended level for high input impedance amplifiers [29]. Each electrode will be referenced to Cz and an electrode placed anterior to Pz will serve as the ground. The electroencephalography (EEG) signal will be amplified with Net Amps 200 amplifier (EGI, Eugene, OR, USA) and a band-pass filter will be set at 0.1 to 100 Hz. The signal will be digitalized at 250 Hz and the data will be recorded with Net Station software (EGI). Recordings will take place in a dimly light electromagnetic-isolated and sound-attenuated room.

EEG recordings will be analyzed using Brain Vision Analyzer software, version 1.05 (Brain Products, Munich, Germany). The data will be filtered off-line with a digital band-pass filter of 0.1 to 15 Hz and 24 dB/octave. Blinks and ocular movements will be corrected with independent component analysis. The data will be re-referenced to average mastoids (A1-A2). The MMN will be determined using a deviant-minus-standard subtraction and by identifying the first peak within the 100 to 350 ms time window of the difference wave. Mean MMN amplitudes will be calculated as a mean voltage of 40 ms intervals, centered at peak latency over the midline and laterally for the fontal, central and parietal regions (that is, F3, Fz, F4, C5, C3, C1, Cz, C2, C4, C6, P5, P3, P1, Pz, P2, P4, P6).

We will use the protocol developed by Ceponiene *et al.*, which has been shown to successfully measure the MMN in newborns [30]. Three blocks of 500 sounds will be presented. The stimuli will be harmonic tones as they have to elicit a robust and reliable signal in adults and children [30]. The standard stimulus, presented in 85% of the trials, will be composed of the fundamental frequency of 500 Hz and its first two harmonics (500, 1,000 and 1,500 Hz). The intensity of the second and third components will be reduced by 3 and 6 dB, respectively. The deviant stimulus, presented in 15% of the trials, will consist of the fundamental frequency of 750 Hz and its first two harmonics (750, 1,500 and 2,250 Hz) with the same reductions of 3 and 6 dB, respectively, for the last two components. All sounds will be presented at 70 dB sound pressure level for a period of 100 ms, with an 800 ms stimulus onset asynchrony.

### General information questionnaire

During the first visit, all participants will be asked to answer questions regarding their and their partner’s professional, economic, educational and health status as well as a family history of hereditary disorders. This questionnaire also documents the details of the participants’ pregnancy.

Monthly visits will include a follow-up questionnaire that will inquire about their health and general habits (for example, alcohol consumption, massages, acupuncture) to ensure they remain eligible to participate in the study as well as to document potential confounders between the two groups.

### Physical activity survey

Exercise habits for the previous year will be assessed using the Kaiser Physical Activity Survey (KPAS) and the first trimester’s exercise habits will be documented with a modified version of the KPAS that was validated for pregnancy [24].

### Daily log

Women will be asked to complete, on a daily basis, an online questionnaire containing 12 questions to document their exercise practice (type, duration, intensity), the quality of their sleep, and their use of medication and supplements.

### Pedometer

Women from both groups will wear a pedometer (Yamax Digi walker SW-200, Tokyo, Japan) on a daily basis for the entire duration of the study. This measure will verify that the exercise sessions performed by the women in the exercise group do not lead to a compensatory augmentation of sedentary behaviors, as has been documented in other exercise intervention studies [31]. Further, pedometer readings will provide an additional measure of physical activity with which to compare both groups.

### Mood questionnaires

Animal studies on the effect of exercise during pregnancy on the newborn’s brain suggest that a high level of maternal anxiety diminishes this effect [12]. Therefore, during their monthly visit, the women will be asked to fill out the Beck Anxiety Inventory [32].

### Accelerometer

All women will wear an ActiTrainer accelerometer (MTI-ActiGraph, Fort Walton Beach, FL, USA) for seven days and three nights during each trimester. This will allow us to verify the accuracy of their daily logs.

### Nutrition journal

Participants will also be asked to fill out a three-day nutrition journal for each trimester. They will be asked to document all of their food and liquid intake with details about the type and quantity of each food item.

### Medical records

A copy of the complete medical records will be obtained from each woman’s obstetrician at the postnatal visit to verify weight gain and standard pregnancy blood test results as well as details of the delivery.

### Preliminary results

As of September 2011, 17 women have given their consent and been randomly assigned to one of the two groups: nine in the exercise group and eight in the control group. Two women from the exercise group and three from the control group were excluded: two for having a miscarriage, one for being pregnant with twins, one for not complying with the experimental protocol, and one for withdrawing consent. Table2 presents the characteristics of all participants.

**Table 2 T2:** Participant characteristics

	**Active group**	**Control group**
	**(n = 7)**	**(n = 5)**
Age (years)		
Mother	29 ± 3	28 ± 4
Father	31 ± 4	31 ± 6
Pre-pregnancy body mass index	24.9 ± 3.7	27.9 ± 5.8
Pre-pregnancy KPAS index	11.62 ± 1.39	10.93 ± 0.65
First trimester KPAS index	9.71 ± 1.19	8.97 ± 1.39
Mother	3 (3)	5 (5)
Father	5 (7)	3 (3)
Revenue ($)	80,000 to 100,000	60,000 to 80,000
(median class)	(40,000)	(40,000)

Data presented as the mean ± standard deviation, except for Education and Revenue, which are presented as the interquartile range. KPAS: Kaiser Physical Activity Survey.

Preliminary results indicate that all women completed the online daily log from week 13 until birth. The active women (n = 7) had journal entries for 23 to 28 weeks and exercised an average of 3.1 ± 0.9 days per week. Sessions lasted from 20 to 90 minutes, at an intensity ranging from 12 to 15 on the Borg scale. Activity type included aerobics, swimming, tennis, elliptical training, hiking, circuit training, Wii sports and rollerblading, with the most common being walking, cycling and water aerobics. Women in the control group (n = 5) had journal entries for 24 to 27 weeks and exercised an average of 0.8 ± 0.6 days per week. Sessions lasted from 20 to 40 minutes, at an intensity ranging from 12 to 13 on the Borg scale. Activities included cycling, water aerobics and swimming, walking being by far the most common.

### Analyses

#### Sample size calculations

To determine the number of participants that need to be included in the present study we completed power analysis from published data obtained by measuring MMN in newborns. MMN studies in newborns report changes in amplitude of up to 260% [30]. However, because no previous study observed the effect we are looking for, we chose to be conservative in our calculations and used an expected difference of 50%. We also used a standard deviation of 56% estimated from the data of frontal electrodes presented in the study by Ceponiene *et al.*, whose MMN protocol we will be using [30]. Thus, to reach statistical significance, 21 women are needed for each group (type I error rate = 0.05 and type II error rate 0.20 = 80% power). Assuming a 30% attrition rate, we want to enroll 30 participants for each group.

#### Statistical analyses

A series of analyses will be completed to determine parity between the groups. Specifically, t-tests will compare sociodemographic status, pre-pregnancy health status, pre-pregnancy and first trimester KPAS scores, nutrition journals, and scores on the anxiety scale between the control and the active groups. We will also complete a qualitative analysis of the medical records including standard blood test results and the details of delivery. A second series of t-tests will verify compliance with the experimental protocol by comparing the data from the daily exercise logs, the pedometers and the accelerometers of both groups.

Separate repeated measure analysis of variance (ANOVA) will be performed on the amplitude and latency data of the recorded brain waves. For each ANOVA, the between-subject factor will have two levels, corresponding to the exercise and control groups and the within-subject factors will be region (frontal, central and parietal) and laterality (left, central and right). Statistical analyses will be carried out using the SPSS software (SPSS 17.0, Chicago, IL, USA). A *P* <0.05 will be considered statistically significant.

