### Methodological strengths

There are several strengths to the proposed protocol. First, we use validated and sensitive neuroelectric measures of the newborn’s brain activity. Also, the prospective randomized design will ensure that the participants in the active and the control groups are comparable for all other characteristics. We will verify group parity by comparing sociodemographic status, pre-pregnancy health status, pre-pregnancy and first trimester KPAS scores, nutrition journals, and scores on the anxiety scale. Further, the same kinesiologist will meet with all of the participants to ensure the standardization of the experimental protocol, including advice and feedback.

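### Parity t-tests at about 21 women per arm cannot show that the groups are comparable, they include measures taken after randomisation, and the printed MMN model uses none of the baseline data

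*Protocol article*

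**What the plan says.** The Statistical analyses section opens: "A series of analyses will be completed to determine parity between the groups". It then names the method and the variables: "t-tests will compare sociodemographic status, pre-pregnancy health status, pre-pregnancy and first trimester KPAS scores, nutrition journals, and scores on the anxiety scale". The only significance threshold given is 0.05.

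Methodological strengths repeats the same list as the way parity will be verified, and states that "the prospective randomized design will ensure that the participants in the active and the control groups are comparable for all other characteristics".

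On timing, the article says:
- Women are allocated after consent and join before week 13, so that the intervention covers the second and third trimesters (Procedure and timeline).
- The Beck Anxiety Inventory is completed at monthly visits (Mood questionnaires).
- A three-day nutrition journal is kept in each trimester (Nutrition journal).

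The MMN amplitude and latency models are written out with group as the between-subject factor and region and laterality as within-subject factors. No covariate is listed, and nothing is said about what follows if a parity test is significant. The General information questionnaire section says that potential confounders will be documented.

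**The concern.** There are three linked problems.

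1. **The test does not answer the question put to it.** A t-test asks whether two population means differ. Randomisation already settles that for variables fixed before allocation. What matters for the MMN comparison is the size of the gap in the women actually analysed, and a P value in a small trial says little about that.

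2. **The list mixes two kinds of variable.** Anxiety and diet measured while one arm is exercising can respond to the exercise. A difference in them is not evidence that the groups started unequal, and a lack of difference is not evidence that they started equal.

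3. **The check leads nowhere.** Prior activity and BMI are collected, but the printed model does not use them. A gap that happens to matter for MMN would stay in the estimate, and any precision these variables could offer is left unused.

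At stake is mainly interpretation: a statement in the trial report that parity was verified would carry more weight than the tests can bear.

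**Working it through.** **Inputs** (Sample size calculations): expected difference 50%; "standard deviation of 56% estimated from the data of frontal electrodes", that is 56%; "type I error rate = 0.05 and type II error rate 0.20 = 80% power"; "21 women are needed for each group"; 30 per group enrolled. Table 2 gives interim means and SDs for 7 active and 5 control women.

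**The plan's own figure.** The standardised difference is 50/56 = 0.893. A two-sided two-sample t-test at 0.05 with 80% power needs 20.7 women, rounded up to 21 per group, and power at 21 is 80.6%. With 30% attrition, 21/0.70 = 30. Both stated figures reproduce. Sidedness is not stated; a one-sided test would need about 16 to 17, so the plan's figure is two-sided.

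**What a parity test can pass.** The standard error of a standardised difference with n per arm is sqrt(2/n). The largest observed gap that stays non-significant is t(0.975, 2n − 2) × sqrt(2/n).
- n = 21: 2.021 × 0.309 = 0.62 SD.
- n = 30 (no attrition): 2.002 × 0.258 = 0.52 SD.

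**How often chance gaps arise.** By the normal approximation with standard error 0.309, one baseline variable differs by more than 0.3 SD in about 33% of randomisations at 21 per arm, and by more than 0.5 SD in about 11%. Gaps of 0.3 to 0.6 SD are therefore not rare, and every one of them passes the test.

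**Illustration from Table 2** (pooled SD, 10 degrees of freedom):

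| Variable | Gap / pooled SD | Size of gap | P |
|---|---|---|---|
| Pre-pregnancy BMI | 3.0 / 4.66 | 0.64 SD | 0.30 |
| Pre-pregnancy KPAS | 0.69 / 1.15 | 0.60 SD | 0.33 |
| First-trimester KPAS | 0.74 / 1.27 | 0.58 SD | 0.34 |

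All three would pass as parity. With 12 women this shows how the test behaves; it does not forecast the final imbalance.

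**Timing of the tested variables.**
- Sociodemographic status, pre-pregnancy health and pre-pregnancy KPAS describe the time before the intervention.
- First-trimester KPAS also describes the pre-intervention period.
- The first-trimester journal may precede the intervention.
- Second- and third-trimester journals and the monthly anxiety scores taken during those trimesters come after randomisation.
- Statistical analyses does not restrict the journals or the anxiety scale to the earliest time point.

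**What a baseline covariate could give.** The documents report no correlation r between a maternal baseline variable and newborn MMN, so r is an assumption shown as a range. The residual SD is 56 × sqrt(1 − r²). Power is for the 50% difference at 21 per arm, in a two-sample approximation that ignores lost degrees of freedom:

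| r | Variance removed | Power |
|---|---|---|
| 0 | 0% | 80.6% |
| 0.2 | 4% | 82.2% |
| 0.3 | 9% | 84.1% |
| 0.5 | 25% | 90.3% |

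With two covariates and r = 0, the error degrees of freedom fall from 40 to 38 and power from 80.6% to 80.5%.

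**Conditional effect of leaving a gap unadjusted.** Given an observed imbalance of 0.5 SD at 21 per arm, the two-sided type I error of the unadjusted test is about 5.8% if r = 0.3 and 8.2% if r = 0.5. Averaged over all randomisations it remains 5%.

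**The case against.** The strongest reply is that an unadjusted comparison of randomised groups is valid, that leaving out covariates is an efficiency choice, and that an analysis plan not shown here may add them. The first two points stand, and they limit the cost to precision and conditional balance. The third is possible. The article nevertheless prints the model in full without a covariate, and the unsound parity rule is stated outright, not left for later.

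A second reply is that the gain may be small. No baseline MMN can exist, the entry criteria restrict BMI to 18 to 25, and nothing in the article links maternal KPAS or BMI to newborn MMN. This also stands: at r = 0.2 the gain is under two points of power.

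Third, the parity tests trigger no action and do not alter the primary test. That is correct, and it confines the harm to interpretation.

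A reader might infer several stronger things that the documents do not support:
- **That low power measures how often imbalance is missed.** The t-test's power at 21 per arm is 16% against a 0.3 SD difference and 35% against 0.5 SD. Those figures refer to a true population difference, which randomisation sets to zero for baseline variables. The 0.62 SD cut-off is the relevant figure.
- **That all nutrition journals are post-randomisation measures.** The first-trimester journal may precede the intervention.
- **That Table 2 shows randomisation failing.** A BMI gap of 0.64 SD in 7 and 5 women is about 1.1 standard errors.
- **That adjustment will raise power to 84% to 90%.** This holds only if r is 0.3 to 0.5, which no figure in the article supports.

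**Conclusion.** The point holds in this limited form. A stated rule, significance testing to establish parity, cannot do its job at this sample size: with 21 per arm it passes every observed gap below about 0.62 SD. It is also applied to anxiety and diet measurements that may be consequences of the intervention. The printed MMN model uses none of the baseline values collected.

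Overall type I error is not affected if all women are compared as randomised. The possible gain from adjustment runs from a loss of about 0.1 percentage point of power (r = 0) to about 10 points (r = 0.5). It rests on an assumed correlation and on a two-sample approximation to the repeated-measures ANOVA.

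The claim that randomisation guarantees comparability is too strong for about 21 women per arm. It is weaker still because women are withdrawn after allocation, including for non-compliance: 5 of the first 17 had been excluded (Preliminary results). Covariate adjustment would not fully repair selection of that kind.

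**What to change.** 1. Replace the parity t-tests with a table of pre-randomisation variables by arm, showing means or medians, spread and standardised differences, without P values.
2. Report anxiety and diet during the intervention separately by arm, labelled as post-randomisation measures, and do not use them as evidence of balance or as adjustment covariates.
3. Name one or two baseline covariates for both the amplitude and the latency model, for example pre-pregnancy BMI and pre-pregnancy or first-trimester KPAS. Include them whatever their observed imbalance, and give the unadjusted result alongside.
4. Do not adjust the main models for gestational age at recording. It depends on the date of birth, which falls after randomisation and could itself be affected by exercise. If it is examined, label it as exploratory and post-randomisation.
5. In Methodological strengths, say that randomisation makes the groups comparable in expectation, and remove the statement that t-tests will verify this.

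The variables in items 1 to 3 are already planned for collection, so the cost is wording, plus about 0.1 percentage point of power if two covariates turn out to be unrelated to MMN. The covariates should be fixed before any MMN data are compared by arm.

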## Discussion

To the best of our knowledge, this is the first randomized controlled trial examining the effects of exercise during pregnancy on the neuroelectric responses of the newborn’s brain. This will provide a direct measure of the influence of physical exercise during pregnancy on the developing brain. The results will contribute to our understanding of the effects of physical exercise during pregnancy on the newborn’s brain and provide some insight on fetal neuroplasticity (that is, how the brain of the fetus is influenced by its environment). Further, if the results of the study confirm our hypothesis, they should influence the way in which health professionals present and discuss exercise with pregnant women. Health professionals will not only encourage pregnant women to exercise for their own health, but also for the benefit of their child’s development.

The findings from the present study will also provide the empirical data to support future research that should concentrate on establishing the ideal volume of exercise needed to achieve the best effects for the newborn and that should aim to identify the biological mechanisms that are responsible for this effect.

### Methodological strengths

There are several strengths to the proposed protocol. First, we use validated and sensitive neuroelectric measures of the newborn’s brain activity. Also, the prospective randomized design will ensure that the participants in the active and the control groups are comparable for all other characteristics. We will verify group parity by comparing sociodemographic status, pre-pregnancy health status, pre-pregnancy and first trimester KPAS scores, nutrition journals, and scores on the anxiety scale. Further, the same kinesiologist will meet with all of the participants to ensure the standardization of the experimental protocol, including advice and feedback.

### Methodological weaknesses

Our protocol also has some limitations that will be taken into account in the interpretation of the data, but that are unlikely to influence the overall pattern of results. Our close monitoring of the participants’ daily exercise via the daily log and wearing of a pedometer will allow us to determine the amount of exercise completed by the experimental group and will allow us to eliminate members of the control group who do not conform to the non-exercising criteria.

We are aware that the MMN is not an intuitive measure for parents about the general functioning of their newborn. However, there are several reasons why we opted for this measure. First, although it may seem abstract, it is associated with specific behavioral processes including sensory memory and cognitive status [18-20]. Second, it is an objective measure of brain functioning in the newborn that is not subject to examiner bias or the child’s state of wakefulness [19]. There are no known behavioral equivalents to this measure that are as sensitive to the newborn’s brain functioning.

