Recent studies in humans have been able to directly investigate functional neural activation in newborns by means of the mismatch negativity (MMN), a component of the auditory event-related potential [18,19]. The MMN wave is elicited by presenting a rare auditory stimulus in a series of repetitive frequent standard sounds. The MMN has been associated with auditory sensory memory and several authors believe that it is an objective measure of the newborn’s cognitive status [20]. For example, earlier and stronger MMN waveforms indicate greater developmental maturity [21], whilst a longer latency and a smaller amplitude are associated with slowed development in children with cleft palate [22] or autism [23].

To further our understanding of the effects of exercise during pregnancy on the development of the human brain, we propose to use a randomized intervention protocol and a direct measure of neonatal brain functioning. Pregnant women will be randomly allocated to an active group or an inactive control group and the latency and amplitude of the MMN evoked-potential will be recorded in their newborns. Given that the main finding from animal studies is an improvement in learning and memory in the offspring of active mothers, we hypothesize that children born to mothers who exercised during their pregnancy will present shorter latencies and larger MMN amplitudes compared with babies born from non-exercising mothers.

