### Procedure and timeline

Women will join the study prior to their 13^th^ week of pregnancy to receive the intervention during the entire second and third trimesters. Gestational age will be determined from the menstrual history. During the first meeting, women will be informed that they will be randomly assigned to the active or control group. Study design is presented in Figure1. They will be clearly informed of the characteristics of each group and of what is expected of them. To avoid any auto-selection bias, they will be assigned to a group only after they have provided their informed consent.

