**Figure 1 F1:**
[figure not shown]
Study design.

Two interventions will be offered: individual recommendations on health habits during pregnancy; and individual recommendations on exercising during pregnancy. To ensure that each group has similar knowledge about health habits during pregnancy and that there is the same amount of one-on-one contact with all participants, both groups will receive the first intervention. Only the active group will receive the second intervention, recommending at least three sessions of exercise per week (see section on Exercise intervention). Participants in the control group will not be given any exercise counseling and will be informed they will be excluded from the study if they exercise more than once per week.

Starting at the beginning of the second trimester, all women will complete a daily log and wear a pedometer for the entire duration of the study. Women from both groups will meet monthly with the same kinesiologist and will receive standardized advice and feedback based on their daily log. During that meeting, all the women will complete a mood questionnaire and the women who are part of the active group will complete an exercise session in order to learn how to characterize their at-home exercise for the daily log. The women who are part of the control group will complete the same exercise session but only once per trimester. During each trimester women from both groups will fill out a three-day nutrition journal and during the second and third trimesters they will wear an accelerometer and a Polar heart rate monitor for seven days and three nights. The timeline of the experimental protocol is presented in Figure2.

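### The MMN is declared free of examiner bias, but its scoring as described leaves room for judgement and no masking of EEG processing is described

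*Protocol article*

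**What the plan says.** Under Methodological weaknesses, the protocol article defends the choice of outcome partly on the ground that "it is an objective measure of brain functioning in the newborn that is not subject to examiner bias".

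The section Primary outcome measures describes how the outcome is obtained:
- Artefact: "Blinks and ocular movements will be corrected with independent component analysis".
- Peak: the MMN is found from the deviant-minus-standard difference wave "by identifying the first peak within the 100 to 350 ms time window of the difference wave".
- Amplitude: "Mean MMN amplitudes will be calculated as a mean voltage of 40 ms intervals, centered at peak latency".

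The Background states a direction for both measures: "children born to mothers who exercised during their pregnancy will present shorter latencies and larger MMN amplitudes".

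The women necessarily know their arm. Before assignment, "They will be clearly informed of the characteristics of each group and of what is expected of them" (Procedure and timeline). One member of staff sees both arms: "Women from both groups will meet monthly with the same kinesiologist". The article does not say who records, processes or scores the EEG, and it does not mention masking of any of them.

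**The concern.** The sentence on examiner bias is broader than the measurement it describes. A newborn cannot react to its mother's allocation, so the response itself is protected. The number that enters the analysis is a different matter, because it comes out of a processing chain. Someone, or some algorithm, has to decide which independent components are artefact and which deflection counts as the first peak. As described, those steps have no component-selection rule, minimum peak amplitude, lead channel, or handling of an absent or doubtful peak.

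A condensed article may well leave such details to a fuller document, and their absence alone would not be worth raising. The point is that the article positively asserts that examiner bias does not arise, and its own description of the processing does not support that. A reader who takes the assertion at face value has no reason to ask for masked scoring. At stake is the validity of the primary outcome in a trial planned on 42 evaluable infants. The Discussion expects a positive result to change how health professionals present exercise to pregnant women.

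**Working it through.** **1. The claim set against the processing steps**

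| Step (Primary outcome measures) | Fixed in the text | Left open in the text |
|---|---|---|
| Recording and filtering | Impedance limit, filters, reference, stimuli | Nothing relevant here |
| Ocular correction | Method (independent component analysis) | Which components are removed |
| Peak | First peak, 100 to 350 ms (350 − 100 = 250 ms wide) | What counts as a peak; manual or automatic; lead channel; absent peak |
| Amplitude | 40 ms mean centred on the peak | Inherits the peak choice |

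One peak decision therefore sets both measures. Accepting an earlier deflection shortens latency by definition. Its effect on amplitude can go either way, so the two measures need not be biased together.

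**2. The plan's own sample size**

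Inputs from Sample size calculations: the authors say "we chose to be conservative in our calculations and used an expected difference of 50" (per cent), with SD 56%, type I error 0.05, power 80% and attrition 30%.

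- Normal approximation: n = 2 × (1.960 + 0.842)² × (56/50)² = 2 × 7.85 × 1.254 = 19.7, so 20 per group.
- Two-sample t-test: 20.7, so 21 per group, with power 80.6% at 21. This reproduces the stated 21. A one-sided calculation gives 16, so the plan is two-sided.
- Attrition: 21 / 0.70 = 30 per group, as stated.

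**3. What a scoring shift would do (assumption only)**

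Suppose that there is no true effect and that scoring adds b percentage points of amplitude to the exercise arm. With 21 per group, df = 40 and the noncentrality is (b/56) / √(2/21) = (b/56) / 0.3086. The rejection rate comes from the noncentral t distribution at the two-sided 5% critical value.

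| Assumed b (points) | b / SD | Noncentrality | Two-sided rejection | In hypothesised direction |
|---|---|---|---|---|
| 0 | 0 | 0 | 5.0% | 2.5% |
| 5 | 0.09 | 0.29 | 5.9% | 4.7% |
| 10 | 0.18 | 0.58 | 8.7% | 8.2% |
| 15 | 0.27 | 0.87 | 13.5% | 13.3% |
| 20 | 0.36 | 1.16 | 20.4% | 20.3% |

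A shift of 10 points is one fifth of the planned 50% difference.

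Limits of the illustration: it uses the two-group comparison behind the sample size, not the planned repeated-measures ANOVA. The 56% is an SD for frontal electrodes only. The article gives no SD for latency, so no matching table can be made for it.

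**The case against.** Several objections have force.

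- **The article may simply be condensed.** Who scores the EEG and whether files are coded could stand in the full protocol. This is right, and the article cannot be read as saying that scoring is unmasked. A reader might infer that the scorers know the allocation, but the text says only that the mothers do, which is unavoidable with exercise.
- **The sentence may only compare the MMN with behavioural assessment.** It is given as a reason for choosing the measure, and what follows it concerns behavioural equivalents. That is a fair reading. A reader might infer that masking was left out because the measure was thought immune to bias, but no such link is written. Even so, the wording is unqualified and reaches further than that comparison.
- **Much of the pipeline is fixed.** Stimuli, filters, reference, search window, the first-peak rule and the averaging interval are all set. A reader might infer that peaks are picked by hand, that the scorer may choose between the first and the largest peak, or that recordings are discarded at discretion. The text says none of these, and it prescribes the first peak. A fully automated rule would shrink the concern considerably.
- **The size of the bias is unknown.** This stands. At the low end of the assumed range the false-positive rate barely moves, from 5.0% to 5.9%.
- **The damage is not permanent.** A reader might infer that such bias could never be undone. The signal is digitised and stored, so component removal and peak scoring can be repeated under code. Only fitting the net and making the recording cannot.

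What remains is a positive statement of freedom from examiner bias that the described processing does not bear out, with no described safeguard beside it.

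**Conclusion.** The point holds in a limited form. The statement on examiner bias is true at most of the infant's response. Component removal and peak identification, as described, are places where knowledge of the arm could influence latency and amplitude in the hypothesised direction, and no masking of EEG processing is described. The documents do not show that any bias occurs and give no basis for its size. On the assumption of a 5 to 20 point shift, with SD 56%, 21 per group and no true effect, the two-sided false-positive rate would be about 6% to 20% instead of 5%. The sample size is unaffected. This is an inexpensive safeguard that should be adopted, or confirmed if it already exists. It is not evidence of a failed design.

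**What to change.** 1. Qualify the sentence under Methodological weaknesses so that it refers to the infant's response and not to the scoring.
2. Store EEG files under a code that does not reveal the arm, with the key held by a team member who does not score.
3. Complete and lock component removal, artefact handling and peak scoring before the key is opened. Identify the first peak by a fixed or automated rule.
4. Re-score under code any files already processed with knowledge of allocation. By September 2011, 7 + 5 = 12 women remained after exclusions, so the backlog at that date could be at most 12 recordings.
5. If masking is already in place, say so in the protocol; only item 1 then needs new wording.

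Cost: file coding, key-holding by someone outside the scoring, and some re-scoring work. There are no extra visits, and the targets of 21 evaluable and 30 enrolled per group stay. The article does not describe EEG staffing, so whether a separate key-holder and a scorer unaware of allocation are already available has to be checked. Coding the files does not mask the person who fits the net and makes the recording, so that exposure remains.
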